## Methods and Analysis

### Trial Design

This study is a double-blind, parallel controlled trial based on a smartphone app. “SPIRIT 2013 Statement Defining Standard Protocol Items for Clinical Trials” is followed in this randomized controlled trial. Each subject will participate in a 12-week Tai Chi and stretching exercises program (Figure 1). Research data will be collected three times. First, sociodemographic information (e.g., age, sex, educational level, and diagnosis certificate or recent medical records from hospitals), and baseline measurement results will be collected. The second data collection will be at 12 weeks after baseline. The third data collection will be at 16 weeks after baseline. The research will start in October 2021 and end in March 2022.

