## Abstract

**Introduction:** Parkinson's disease (PD) is a common neurodegenerative disease that seriously impairs patients' quality of life, and increases the burden of patients and caregivers. Both drugs and exercise can alleviate its motor and non-motor symptoms, improving the quality of life for PD patients. Telehealth, an increasingly popular tool, makes rehabilitation accessible at home, overcoming the inconvenience of traffic and scheduling. Care-PD is a phone application designed for rehabilitation training, which provides Tai Chi and stretching exercises through tutorial videos as well as an online evaluation system. In this protocol, we will explore the efficacy of Tai Chi and stretching exercises as a PD rehabilitation therapy based on the smartphone application Care-PD.

**Methods and Analysis:** A double-blind, parallel randomized controlled trial will be conducted in this study. The recruitment, intervention, and evaluation processes will be implemented through the Care-PD application. Persons with PD will fill out questionnaires on Activities of Daily Living (ADL), upload the latest case report, and sign the informed consent form in the application. Afterward, doctors and researchers will screen and enroll 180 participants who will be randomly (1:1:1) assigned to Tai Chi group, stretching exercises group, or control group. The subjects will participate in a 1-h exercise session three times per week for 12 weeks, ending with another 4 weeks of follow-up study. Each exercise session includes 10 min of warm-up, 45 min of exercise, and 5 min of cool-down. The primary outcomes are Motor Aspects of Experiences of Daily Living and the 39-item Parkinson's disease Questionnaire. The secondary outcomes include the 9-item Wearing-Off Questionnaire, the Freezing of Gait Questionnaire, the Caregiver Strain Index, Non-motor Experiences of Daily Living, ADL, and Morse Fall Scale. All assessments will be performed at baseline, week 12 and 16.

**Discussion:** Care-PD integrates subject recruitment, intervention, and evaluation, providing a new perspective on clinical rehabilitation for persons with PD. This study will evaluate the efficacy of Tai Chi and stretching exercises on patients' quality of life and disease progression based on a smartphone application. We aim to provide a new rehabilitation training platform for persons with PD.

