### Recruitment

The Care-PD app includes eight modules (37). In this study, we mainly use the modules of Research and Recruitment, Self-Assessment, Adverse Report, Exploratory Research, and Medication Recording. The Research and Recruitment module is designed to recruit persons with PD online, while the Self-Assessment module simulates the evaluation process. The Adverse Report module is used for recording adverse events. The Exploratory Research module simulates exercise intervention, providing both Tai Chi and stretching exercises videos. The Medication Recording module is used for recording patients' daily medicine use.

The Care-PD app will be supervised by neurologists from Shanghai Tongji Hospital and researchers from the Shanghai University of Sport. The patients will complete the form on sociodemographic information, ADL, and sign the informed consent form. At the same time, the administrators, including doctors and researchers, will evaluate and decide whether the subjects fit the criteria. After evaluation, eligible subjects will enter the Research and Recruitment module and be randomly divided into three groups: Tai Chi group, stretching exercises group, and control group (Figure 2). The administrators play an important role in the intervention. First, they evaluate and screen the basic information of subjects. Second, they assist subjects or their caregivers with the installation and registration of the Care-PD app. Last, they supervise the participants' exercise progress and serve as training instructors. All assessments are completed by patients with or without the assistance of the caregivers. Participants can contact the administrators at any time during the intervention period.

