### Allocation and Randomization

Randomization is performed with online software (http://www.randomization.com). Participants will receive a number corresponding to Tai Chi group, stretching exercises group, or control group in a randomized controlled table. The allocation result is hidden using a sealed envelope (sequential number). No researcher involved in this study will perform randomization. Researchers responsible for randomization are not involved in the recruitment of subjects, exercise intervention, or outcome evaluation. Similarly, subjects are instructed to withhold the allocation result.

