### Control Group

The modules of the Care-PD app available to the control group are consistent with those of Tai Chi group and stretching exercises group except for training programs. The control group will have access to the Medication Recording module but not the exercise videos. After the trial, Tai Chi and stretching exercises videos will be available to all participants in the control group.

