### Adverse Events

Subjects need to record daily adverse events, including falls, muscle soreness, injuries, and dizziness. Once an adverse event occurs, they should contact the doctors or researchers as soon as possible and call the emergency number if necessary. To ensure that subjects complete the record of adverse events, the doctors and the researchers will verify the record every time they contact the participants.

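### The trial is labelled double-blind, but neither participants nor the raters of its outcomes can be blind to arm, and comparisons with control combine exercise with contact and expectation

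*Protocol article*

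**What the plan says.** The label appears twice in the protocol article: in the Abstract ("A double-blind, parallel randomized controlled trial will be conducted in this study") and in Trial Design ("This study is a double-blind, parallel controlled trial based on a smartphone app"). Neither place says who is blinded or how.

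Allocation and Randomization describes sequentially numbered sealed envelopes and randomising staff who take no part in recruitment, intervention or evaluation. It adds: "Similarly, subjects are instructed to withhold the allocation result".

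On delivery, the Intervention section has participants join a supervised and recorded video conference with the camera on, three times a week for 12 weeks, one hour each time. The Tai Chi Group section names a Tai Chi specialist as remote supervisor, and Adherence Promotion has coaches supervising by video. For control, "The control group will have access to the Medication Recording module but not the exercise videos", and "After the trial, Tai Chi and stretching exercises videos will be available to all participants in the control group".

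On outcome rating, the Recruitment section says: "All assessments are completed by patients with or without the assistance of the caregivers". Outcome Assessment repeats that patients or caregivers fill in the questionnaires. The Discussion accepts that online questionnaires are the only means of assessment.

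The Introduction's hypothesis is that Tai Chi is superior to stretching. The analysis section also plans a three-arm between-group comparison that includes control.

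**The concern.** Double-blind is a specific claim about bias protection. It matters most where outcomes are subjective, and here every efficacy outcome is a rating by the patient or caregiver, including both primaries (M-EDL and PDQ-39). If the rater knows the arm, hope or disappointment can move the score without any change in the disease. A reader who relied on the label would credit the trial with protection it does not have. The limitations in the Discussion mention questionnaire-only assessment but not the absence of blinding.

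The arms also differ in supervised contact. A difference between an exercise arm and control therefore cannot be assigned to the exercise itself.

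**Working it through.** **Is either side of the label tenable?** No stated figure is involved, so the statements are set side by side.

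| Role | What the article says | Blind to arm? |
|---|---|---|
| Participant | Told to keep the allocation to themselves, which presupposes knowing it; either does live Tai Chi, does live stretching, or has no exercise videos until the trial ends | No |
| Trainer | Tai Chi specialist and coaches supervise by video | No |
| Outcome rater | The patient, with or without the caregiver | No for the patient; for the caregiver this is inferred from the role, since caregivers help clear the exercise space |
| Randomising staff | Separate from recruitment, delivery and evaluation; sealed envelopes | This is concealment before assignment, not blinding after it |
| Analyst | Not described | Unknown |

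Participant and rater are the same person, or a household pair, for all eight questionnaires. Even a masked analyst would not make those ratings blind.

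**Contact.** From the Intervention section: 3 sessions per week × 12 weeks = 36 sessions; 36 × 1 h = 36 h in each exercise arm. The Control Group section describes no equivalent.

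**Illustration of what an expectation shift could do.** The size of the shift is assumed, since the article gives none. Inputs:

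- True exercise effect 0; two-sided alpha 0.05; one exercise arm against control.
- Shift d in SD units; n per arm of 60 (planned) or 60 × (1 − 0.35) = 39 (the upper dropout rate in Sample Size).
- A simple two-group comparison of means with a normal approximation, not the planned mixed-model repeated-measures ANOVA.

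Formula: z = d / √(2/n); P(significant) = Φ(z − 1.96) + 1 − Φ(z + 1.96).

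- n = 39, d = 0.2: z = 0.2/0.2265 = 0.883; P = 0.143
- n = 39, d = 0.3: z = 0.3/0.2265 = 1.325; P = 0.263
- n = 60, d = 0.2: z = 0.2/0.1826 = 1.095; P = 0.195
- n = 60, d = 0.3: z = 0.3/0.1826 = 1.643; P = 0.376

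Across a wider assumed range, d = 0.1 gives 7.3% (n = 39) and 8.5% (n = 60), and d = 0.5 gives 59.8% and 78.2%. The nominal rate is 5%.

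**The case against.** Participants cannot be blinded to exercise versus no exercise, and the article describes the arms and the self-reporting openly, so an attentive reader can see the true position. The hypothesis already compares two arms with the same session structure, and the article never claims to separate exercise from contact. If the target is the whole supervised package, an expectation effect is part of the effect and the rates above are not false positives. All of this stands. It limits the problem to a wrong label, an unstated limitation and the reading of comparisons with control. It does not make the label true.

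Some stronger readings are tempting but not supported:

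- *Control has no contact.* Control is assessed at weeks 0, 12 and 16, has the same app modules apart from training, and may contact the administrators at any time. The control panel of Figure 3 is not shown. The text supports only that no supervised sessions are described.
- *Encouragement goes only to the exercise arms.* Adherence Promotion promises it to the subjects without limiting it by arm.
- *Adverse events are checked 36 times in the exercise arms and never in control.* Adverse Events says "the doctors and the researchers will verify the record every time they contact the participants", but whether sessions count as such contacts is unclear. The Tai Chi Group section excludes researchers from supervising that programme, while Recruitment and Intervention give administrators (doctors and researchers) and researchers a part in it. All participants must also keep a daily record. Unequal verification is possible, not established.
- *The title is wrong too.* It is not in the text available for this review and cannot be judged.

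**Conclusion.** The point holds in this form: the article claims a design property that the trial does not have. Neither participant nor outcome rater is blind for either primary outcome or any secondary one, and what is described is allocation concealment. This conclusion rests on the article's own statements; only the caregivers' knowledge of the arm is inferred.

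A difference from control measures exercise, contact and expectation together. The size of the non-exercise part is unknown. Under an assumed shift of 0.2 to 0.3 SD and no true effect, significance would occur in about 14 to 26% of trials at 39 per arm and about 19 to 38% at 60 per arm. These figures show sensitivity and are not an estimate of bias in this trial.

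A reader might infer that the Tai Chi versus stretching comparison fails for the same reason. It does not fail on contact, because the session structure and video supervision are matched. Expectation may still differ between the two, so that comparison is also open-label.

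**What to change.** 1. In the Abstract and Trial Design, and in the title if it carries the label, replace double-blind with: open-label to participants and trainers, with concealed allocation. Claim masking of the analyst only if arms are actually coded for analysis.
2. Add unblinded patient- or caregiver-reported outcomes to the limitations in the Discussion.
3. Rest the efficacy conclusion on the stated hypothesis, Tai Chi versus stretching, noting that expectation may still differ. State that differences from control are effects of the whole supervised package.
4. Base between-arm comparisons of adverse events on the daily self-records required of everyone, because staff verification may differ by arm.
5. Reconcile the Recruitment, Intervention and Tai Chi Group sections on whether researchers take part in supervising the Tai Chi sessions.

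The cost is mostly wording, plus coded arm labels if analyst masking is to be claimed. Sample size, visits and questionnaires are unchanged. The downside is a less favourable design label.

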**Figure 1 F1:**
[figure not shown]
Workflow of the study. Eligible subjects will be randomly divided into Tai Chi group, stretching exercises group, and control group, and evaluated three times.

### Participants

We will conduct online recruitment (e.g., WeChat) and post advertisements in communities and hospitals to recruit more participants. The researchers in charge of recruitment will remotely guide participants through the registration process. The subjects with PD interested in our research will sign up for the phone app.

Before enrollment, participants will be comprehensively evaluated based on the following items: (1) diagnosis certificate or recent medical records uploaded in Care-PD (Supplementary Figure 1A), (2) Activities of Daily Living (ADL) index scoring (35, 36), and (3) remote video conference evaluation conducted by professional neurologists. The video conference utilizes two cameras (the primary camera and the secondary camera) to remotely monitor the subjects' performance.

We plan to recruit 180 participants who will be divided into three groups using a 1:1:1 randomization formula: Tai Chi group, stretching exercises group, and control group. Every eligible subject will sign the informed consent form in the app (Supplementary Figure 1B).

The inclusion criteria for subjects with PD are:

(1) Diagnosis of idiopathic PD,(2) Age of 40 to 75 years with the ratio of males to females ~1–1,(3) Currently receiving pharmacologic treatment (levodopa) under stable conditions,(4) Scoring over 55 in ADL index,(5) Willingness to cooperate with treatment and sign the informed consent form.

The exclusion criteria are:

(1) Diagnosis of typical PD,(2) Inability to stand for 45 min or complete exercise training,(3) High risk of falls in the next 6 months indicated by Morse Fall Scale (MFS) (37),(4) Severe cognitive or mental disorders verified through remote video conference with the help of caregivers,(5) Inability to use a smartphone or lack of assistance from family members or caregivers to do so.

### Recruitment

The Care-PD app includes eight modules (37). In this study, we mainly use the modules of Research and Recruitment, Self-Assessment, Adverse Report, Exploratory Research, and Medication Recording. The Research and Recruitment module is designed to recruit persons with PD online, while the Self-Assessment module simulates the evaluation process. The Adverse Report module is used for recording adverse events. The Exploratory Research module simulates exercise intervention, providing both Tai Chi and stretching exercises videos. The Medication Recording module is used for recording patients' daily medicine use.

The Care-PD app will be supervised by neurologists from Shanghai Tongji Hospital and researchers from the Shanghai University of Sport. The patients will complete the form on sociodemographic information, ADL, and sign the informed consent form. At the same time, the administrators, including doctors and researchers, will evaluate and decide whether the subjects fit the criteria. After evaluation, eligible subjects will enter the Research and Recruitment module and be randomly divided into three groups: Tai Chi group, stretching exercises group, and control group (Figure 2). The administrators play an important role in the intervention. First, they evaluate and screen the basic information of subjects. Second, they assist subjects or their caregivers with the installation and registration of the Care-PD app. Last, they supervise the participants' exercise progress and serve as training instructors. All assessments are completed by patients with or without the assistance of the caregivers. Participants can contact the administrators at any time during the intervention period.

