### Intervention

All subjects will take medicine according to prescriptions and record the use of medicine in the Medication Recording module (37). Exercise videos of Tai Chi and stretching exercises will be uploaded to the Exploratory Research module in advance. Each Tai Chi and stretching exercises session consists of 10 min of warm-up, 45 min of exercise, and 5 min of cool-down. The program will last for 12 weeks, with each week containing three sessions of 1-h long exercises, followed by 4 weeks of follow-up without intervention. To ensure safety, subjects will be asked to clear up the surroundings in advance with the assistance of caregivers.

In addition, WeChat and Tencent Meeting will be used for communicating with the participants. Before each intervention, Care-PD will send a notification as well as a text message to remind the participant to exercise according to schedule. During the intervention, a video conference will be initiated that the subjects then join with the camera on. The entire process of the exercise intervention will be supervised and recorded. The researchers will inform subjects on the techniques of exercise, safety precautions, and emergency measures in case of adverse events. At the end of the intervention, the researchers will remind the subjects to log in and inquire about changes in their physical and psychological conditions. The specific plan of intervention is shown in Figure 3. The detailed moves of Tai Chi and stretching exercises are presented in Table 2.

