### Tai Chi Group

Tai Chi group joins a 12-week Tai Chi training program that utilizes the Medication Recording module in Care-PD to instruct the use of medicine. Simple Tai Chi, designed by martial art specialists based on the characteristics of PD symptoms, includes 10 exercises: (1) the preparatory and rising, (2) lifting, (3) leaning, (4) spine, (5) wrist-wrapping, (6) palming, (7) freestanding, (8) flying, (9) opening and closing, and (10) retracting positions. The total duration of Tai Chi is 18 min and 55 s. The detailed moves of Tai Chi have been introduced in a previous article (34). The program is remotely supervised by an experienced Tai Chi specialist without the involvement of researchers. The aim of the first 2 weeks of intervention is for the subjects to master every move of the exercise. From week 3 to 12, subjects will perform the full Tai Chi exercise 2–3 times, with 5–10 min of rest in between depending on the fluency of exercises. The number of repetitions is determined by the physical fitness of subjects.

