### Adherence Promotion

Participant adherence is measured by the rate of recruitment and retention, online time, and other adherence performance. Coaches and doctors are responsible for supervising and managing the participants:

(1) Before each exercise, the attendance rate will be counted.(2) During the exercise, log-in time in the video conference and Care-PD app will be recorded, respectively. Moreover, coaches will supervise the exercise through video conference which will be recorded and reviewed subsequently.(3) Before and after the intervention, the time spent on filling online questionnaires will also be recorded.

In addition, the subjects will receive verbal encouragement and humanistic care. We plan to reward participants for following instructions to improve their adherence to the program. Immediate results from the assessment module in the application will also create a positive feedback loop that stimulates participant adherence.

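### One named group both decides eligibility and instructs the exercise sessions; the sections disagree on who trains, and no rule separates screeners from instructors

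*Protocol article*

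**What the plan says.** The article describes the staff roles in five places.

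- **Recruitment, on screening:** "the administrators, including doctors and researchers, will evaluate and decide whether the subjects fit the criteria".
- **Recruitment, on training**, in the list of the same administrators' duties: "Last, they supervise the participants' exercise progress and serve as training instructors".
- **Tai Chi Group:** "The program is remotely supervised by an experienced Tai Chi specialist without the involvement of researchers". The Stretching Exercises Group section has no matching sentence.
- **Intervention**, written for both exercise arms: "The researchers will inform subjects on the techniques of exercise, safety precautions, and emergency measures in case of adverse events".
- **Adherence Promotion:** "Coaches and doctors are responsible for supervising and managing the participants".
- **Allocation and Randomization:** the allocation is concealed in sequentially numbered sealed envelopes, and "Researchers responsible for randomization are not involved in the recruitment of subjects, exercise intervention, or outcome evaluation".

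**The concern.** There are two linked problems.

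The first is consistency. A study team reading these sections could not tell who may run a session. Administrators, researchers, a specialist from outside the research team, and coaches with doctors are each given some part of instruction or supervision.

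The second is the missing separation. Someone who instructs a session knows the arm of everyone in it. If that person also rules on later candidates, the ruling may be made with knowledge of how the arms are filling. Several criteria under Participants call for judgement: stability on medication, ability to complete the training, and severity of cognitive or mental disorder. What is at stake is concealment at the point of entry. A screener who can partly predict the next arm could, knowingly or not, admit, delay or decline a borderline candidate accordingly.

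**Working it through.** The plan states no figure on this point, so there is none to reproduce. The check has three parts.

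**1. The role statements side by side**

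| Section | Who | Task |
|---|---|---|
| Recruitment | Administrators (including doctors and researchers) | Decide eligibility |
| Recruitment | The same administrators | Supervise progress, instruct training |
| Tai Chi Group | Tai Chi specialist, researchers excluded | Supervise the Tai Chi program |
| Intervention | Researchers | Inform subjects on technique and safety |
| Adherence Promotion | Coaches and doctors | Supervise and manage participants |
| Allocation and Randomization | Randomizers | Kept out of recruitment, intervention and evaluation |

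Recruitment conflicts with Tai Chi Group, because a group containing researchers instructs in one and researchers are excluded from supervision in the other. Intervention and Adherence Promotion fit poorly with both. Doctors appear as screeners in Recruitment and as supervisors in Adherence Promotion, so the overlap would remain even if the Recruitment sentence alone were changed. The last row separates randomizers from everyone else. No row separates screeners from instructors.

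**2. Could screening and training overlap in time?**

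Trial Design gives October 2021 to March 2022, and each participant needs 16 weeks.

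- Longest reading, 1 October to 31 March: 181 days / 7 = 25.9 weeks; 25.9 − 16 = 9.9 weeks for enrolment.
- Shortest reading, 31 October to 1 March: 121 / 7 = 17.3 weeks; 17.3 − 16 = 1.3 weeks.

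Both are shorter than the 12-week program. With rolling starts, early participants would still be training while late candidates are screened. The article does not say whether entry is rolling or in one batch.

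**3. How predictable would the next arm be?**

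Inputs are three arms at 1:1:1 and 180 participants (Participants section). Two things are assumed: the blocking scheme, and an observer who knows every earlier allocation in all three arms. The observer guesses the arm with most places left in the block. The chance of being right at each step is (largest number of places left in any arm) / (places left in the block), averaged over all orderings.

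- Simple randomization: 1/3 = 33.3% at every step.
- Blocks of 3: (1/3 + 1/2 + 1) / 3 = 0.611.
- Blocks of 6: the expected chances at the six steps are 1/3, 2/5, 1/2, 8/15, 3/5 and 1. Their sum is 101/30 = 3.367, and 3.367 / 6 = 0.561.
- Larger blocks come from the same recursion.

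An allocation is certain when all places left in the block belong to one arm. In blocks of 3 that is the last place, 1/3 of 180 = 60. In blocks of 6 it is the last place always and the fifth with probability 1/5, so 1.2 / 6 = 0.20, and 0.20 × 180 = 36.

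| Assumed scheme | Correct guess | Certain allocations of 180 |
|---|---|---|
| Simple | 33.3% | 0 |
| One block of 180 | 38.8% | about 1.5 |
| Blocks of 12 | 51.2% | 20 |
| Blocks of 6 | 56.1% | 36 |
| Blocks of 3 | 61.1% | 60 |

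**The case against.** The best defence is that the article uses a team label loosely. The administrators are a group, and nothing says that each member both screens and trains. Elsewhere tasks are divided: neurologists carry out the video evaluation, certain researchers handle recruitment, a specialist supervises Tai Chi, and coaches watch sessions. The specialist might be a non-researcher member of the administrator team, and informing subjects on technique might mean a briefing. Some criteria (age, ADL score, Morse Fall Scale) are numeric or scale-based and leave less room for discretion. This defence softens the contradiction without removing it: the Recruitment sentence assigns both duties to the group as a whole, and no sentence limits either duty to a subset.

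A reader might also infer more than the text supports.

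- *Screeners know earlier allocations, so selection bias follows.* This needs rolling entry, the same individuals in both roles and a restricted sequence. The article states none of these. Knowing past allocations does not reveal the next one under simple randomization. An unstated block size in an article is not itself a fault.
- *Researchers are excluded from all training.* The exclusion concerns supervision of the Tai Chi program only.
- *Remote recruitment means staff must open the envelopes, which is a breach.* The article does not say who opens them. Opening the next numbered envelope after enrolment is how the method normally works, and the independent randomizers could do it.
- *Any resulting baseline differences could not be adjusted for.* Both primary outcomes are measured at baseline, so measured differences can be handled in the analysis.

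**Conclusion.** The point stands in a limited form. Two parts rest on the text alone: the sections disagree on who delivers and supervises training, and no rule separates those who judge eligibility from those who instruct. The effect on concealment is conditional. If entry is rolling and the same people do both jobs, the chance of guessing the next arm runs from 33% (no added predictability) to 61% (blocks of 3). The upper figures also need full knowledge of all three arms. It is worth correcting because the arrangement is written into the plan and a safer one is readily available. It is not evidence that allocation would be biased.

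**What to change.** 1. State that staff who decide eligibility do not instruct or supervise exercise sessions in either exercise arm, and that the coaches or specialist already named do so.
2. Amend Recruitment, Intervention, Tai Chi Group and Adherence Promotion to agree with this. Adherence Promotion must be included, because doctors both screen and supervise as the text stands. Add the matching sentence for the stretching arm.
3. Record the eligibility decision and the baseline questionnaires as final in Care-PD before the independent randomizer releases the allocation. Participant Timeline already places screening and baseline before group assignment, so this step enforces an existing order. The envelopes can stay.

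The change needs no extra participants or visits. It reassigns roles among staff already named and adds a step in an app already in use. The small downside is less flexibility in who covers a session.
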